### Data handling

Data used in this study will be collected and managed using the software *“Research Electronic Data Capture”* (REDCap) [12] hosted on the servers of the Hospital Sírio-Libanês. REDCap is a safe software web-based and designed to capture information, providing: 1) an intuitive interface for validated data collection; 2) audit trails for screening data manipulation and export procedures; 3) automated export procedures for continuous data downloads to common statistical packages; 4) procedures for importing data from external sources [12]. REDCap is a secure, browser-based web application widely used by researchers for survey data collection. REDCap offers unique features that can be used to conduct rigorous randomized controlled trials (RCTs).

Research assistants will have a tablet with online access to the study database through login and password to fill out the screening, application, and signature of the Informed Consent Term through the functionality of REDCap eConsent framework, and complete the assessment data during the project.

Data to be collected at baseline include age, sex, social and demographic parameters, clinical parameters, detailed medication history, functionality, cognition, quality of life, mobility in life spaces, gait speed, muscle strength, fear of falling, and fall history.

### Randomization and blinding

The process of randomization will be carried out by the software REDCap (automatically, without contact with the researcher) after the baseline evaluation. Subjects will be allocated to one of the intervention groups (1:1:1), which will have the same number of participants each: walking aid (WA) group; walking aid with telemonitoring (WAT) group; control group. The WA group will be trained for the use of a walking aid and receive guidance on safe gait but will not receive telemonitoring. The WAT group will receive training for the use of a walking aid, guidance on safe gait, and telemonitoring. The control group will receive only guidance on safe gait.

This study will be blind for the researchers involved in the post intervention assessments and the researcher who will analyze the data. Also, the data will be analyzed by a researcher who is not involved in the interventions nor the assessments.

### Procedures

#### Recruitment

The recruitment will be carried out by a researcher in the Geriatric ED of the Hospital Sírio-Libanês (São Paulo, Brazil), who will actively search for eligible subjects or will be called by a physician or a nurse on duty.

#### Screening

The volunteer participants will undergo a screening process to ensure the eligibility criteria for this study. In this step, the participants are going to be interviewed for data collection (social, demographic, clinical, and medication history). One of the exclusion criteria is delirium, which is going to be evaluated by the Confusion Assessment Method (CAM), a fast instrument that can be used by clinical physicians and researchers without the need for a psychiatric qualification [13].

#### Assessment moments

Baseline assessment will be carried out before randomization and interventions. Assessment of gait speed and fear of falling will be repeated immediately after the intervention. Fear of falling, life-space mobility, functionality, quality of life, fall history, cognition and mood assessments will be repeated 3 and 6 months after intervention by a telephone interview or video call.

#### Mobility in life-space

Mobility in life space will be a secondary outcome of the study and will be assessed by the LSA, which allows the characterization of mobility in life-spaces (other rooms of your home besides the room where you sleep; to an area outside your home, places outside your neighborhood but within your town; and to places outside your town), specifically frequency, need for mobility aids and the help of third party in the last 4 weeks [14]. Four indicators are calculated (with the highest scores indicating greater life space):

Independent life-space: the highest life-space level attained without help from a person or mobility aid.Life-space using equipment: the highest life-space level attained when a mobility aid was used, without help from a person.Maximal life-space: the highest life-space level attained with the help of a person or mobility aid.Composite score: encompasses distance, frequency, and level of independence, with a range from 0 to 120.

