Finally, new technologies have been developed to improve health care, including telemonitoring. Telemonitoring is defined as the use of information technology and telecommunications for remote health care [9] and its main advantages are reducing unnecessary visits and home visits, reducing the risk of infections, monitoring the rehabilitation process, and improving patient compliance [10]. However, most studies related to telemonitoring are carried out with patients who have chronic diseases. Also, there are no data on the effects of an intervention encompassing gait devices, associated or not with telemonitoring, to improve the mobility of older patients admitted to the ED despite recommendations from international societies and the Geriatric Emergency Department Accreditation (GEDA) accreditation [3].

The hypothesis of the study is that the provision of walking aids enhances mobility in living spaces and will have a significant impact on fear of falling, functionality, and quality of life. Therefore, this study aims to evaluate the efficacy of a program of training and provision of walking aids, associated or not with telemonitoring, on fear falling, mobility, quality of life, and risk of falls up to 3 and 6 months in older adults cared for in an ED. In addition, we hypothesize that fear of falling may be correlated with lower scores in mobility, quality of life, and risk of falls.

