#### Secondary outcomes

Secondary outcomes will include mobility, functionality, quality of life, mood, cognition, and occurrence of falls in three months.

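### Independent and equipment life-space move with use of the assigned walking aid itself, and the composite may too, so they do not compare mobility fairly between arms

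*Protocol article*

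**What the plan says.** The Introduction of the protocol article states the hypothesis that "the provision of walking aids enhances mobility in living spaces". Under Secondary outcomes, "Secondary outcomes will include mobility, functionality, quality of life, mood, cognition, and occurrence of falls in three months"; the section Mobility in life-space makes the LSA a secondary outcome.

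That section says the instrument records, for each life-space, "specifically frequency, need for mobility aids and the help of third party in the last 4 weeks". Four indicators are derived, and on each a higher score is read as greater life space:

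- "Independent life-space: the highest life-space level attained without help from a person or mobility aid"
- "Life-space using equipment: the highest life-space level attained when a mobility aid was used, without help from a person"
- "Maximal life-space: the highest life-space level attained with the help of a person or mobility aid"
- "Composite score: encompasses distance, frequency, and level of independence, with a range from 0 to 120"

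No item weights for the composite are given. Under Randomization and blinding, the walking-aid (WA) and walking-aid-plus-telemonitoring (WAT) groups are trained to use an aid, and controls get safe-gait guidance only. Under Telemonitoring, the WAT group is repeatedly reminded of the importance of its device. The Discussion relies on the LSA to identify controls who start using a device.

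**The concern.** Allocation is meant to change whether a person walks with an aid. Two of the four indicators are defined by whether an aid was used, and the composite contains a component that may depend on it. On these measures a difference between arms can show that people took up the aid, whether or not they go further or more often. The Discussion's use of the LSA to detect aid use in controls confirms that the instrument registers it, yet nothing in the article recognises the consequence for the arms that receive the device.

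At stake is the reading of the life-space hypothesis. A lower independent score in the aid arms could be taken as lost mobility, and a higher equipment score as gained mobility, when both reflect the same trips made with a cane. The WAT-versus-WA contrast is exposed in the same way if telemonitoring improves adherence to the device.

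**Working it through.** **1. The level indicators, from their definitions.** Take a participant whose trips reach level 4 (an illustrative level) and do not change. Compare making them all unaided with making them all with the aid and no helper.

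| Indicator | All trips unaided | Same trips, always with aid | Shift |
|---|---|---|---|
| Independent | 4 | lowest value, if the aid is used everywhere | down |
| Using equipment | lowest value | 4 | up |
| Maximal, read as with or without help | 4 | 4 | 0 |
| Maximal, read literally as assisted movement only | lowest value | 4 | up |

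The first two shifts need no assumption about scoring. The last two rows show that maximal life-space is neutral only if unaided movement counts, which its wording does not say.

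**2. The composite, under an assumed scoring.** The only figure in the article is the range 0 to 120. Assume composite = sum over levels of (level × frequency × independence), with levels 1 to 5, frequency 1 to 4 (0 if not visited), independence 2 for unaided movement and *m* for aided movement. The unaided maximum is (1+2+3+4+5) × 4 × 2 = 120, which agrees with the stated range. This checks the unaided end only and says nothing about *m*.

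If the aid is used at every level and movement is identical, the proportional fall is 1 − *m*/2, whatever the movement profile or number of levels:

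| *m* | 2.0 | 1.75 | 1.5 | 1.25 | 1.0 |
|---|---|---|---|---|---|
| Fall | 0% | 12.5% | 25% | 37.5% | 50% |

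In points at *m* = 1.5:

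- All five levels daily: 15 × 4 = 60; 60 × 2 = 120 falls to 60 × 1.5 = 90.
- Moderate mover (frequencies 4, 4, 3, 2, 0): 4 + 8 + 9 + 8 = 29; 58 falls to 43.5.
- Restricted mover (frequencies 4, 3, 1, 0, 0): 4 + 6 + 3 = 13; 26 falls to 19.5.
- Moderate mover using the aid only from level 2 outward: 4 × 2 + 25 × 1.5 = 45.5, a fall of 12.5 points.

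**3. Arm level.** For moderate movers at *m* = 1.5, the fall per new full-time user is 58 − 43.5 = 14.5 points. If a share *s* of the arm become such users with no change in movement, the arm mean shifts by −14.5 × *s*: −3.6 at 25%, −7.3 at 50%, −10.9 at 75% and −14.5 at 100%.

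**4. The opposite direction.** The LSA also records personal help. Assume, for illustration, that movement with a helper is weighted 1.0. A moderate mover who replaces the helper with an aid goes from 29 × 1.0 = 29 to 29 × 1.5 = 43.5, a rise of 14.5 points for the same trips. Under these weights, equal numbers of such participants and of previously unaided ones would cancel (−14.5 + 14.5 = 0). The net shift in an arm depends on a baseline mix that the article does not give.

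**The case against.** The strongest case against concerns the composite. One might infer that it is biased against the aid arms by construction, by 25%. The article does not support that. It gives no weights, the 0 to 120 range does not identify the aided multiplier, and 25% is one point in a range that includes zero. Every participant must have an indication for a mobility aid, so some may rely on a helper at baseline and could gain by switching. Existing aid users are not excluded and lose nothing further unless they use the aid more. This objection stands: for the composite, neither the size nor the net sign is known.

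Second, one might infer that any participant who complies loses independent life-space. That also goes too far. The indicator is the highest level reached, and the LSA looks back 4 weeks, so a part-time user who makes one unaided trip to that level keeps it. The fall requires the aid on every trip to that level.

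Third, a reader might fault the article for not choosing one of the four indicators. A condensed article may leave that to the full protocol or analysis plan, so the omission is not itself a defect. Nor do a lower independent score and a higher equipment score contradict each other; they are labelled separately and, since all four are calculated, the pattern would be visible. What remains is that the article defines indicators whose values depend on the assigned device and reads all of them as extent of life space.

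Finally, independence is a legitimate construct, and true gains in range or frequency could offset a penalty. Neither point makes an indicator defined by aid use a fair measure of mobility between arms whose aid use is set by allocation.

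**Conclusion.** The concern holds for independent life-space (down) and life-space using equipment (up). Both follow from the article's definitions when the same trips are always made with the aid, so neither is a fair between-arm efficacy measure. The composite may shift as well: down for those who previously moved unaided, possibly up where the aid replaces a helper. Under the assumed structure with 2 for unaided movement, the downward shift for identical movement made wholly with the aid is 0% to 50% for aided multipliers from 2.0 to 1.0, and 25% at 1.5. All of these composite figures rest on assumed weights.

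It may be tempting to treat maximal life-space as already aid-neutral. Read literally, it counts assisted movement only and would rise with aid use, so its definition must be clarified first.

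The effect is confined to participants who newly use an aid or use it more. Life-space is a secondary outcome, and the primary outcome (FES-I) is unaffected. The point is worth correcting because life-space is part of the stated hypothesis and the correction is cheap.

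**What to change.** - Reword maximal life-space as the highest level attained with or without help from a person or equipment, and name it as the aid-neutral life-space comparison between arms.
- If the composite is also compared, add a sensitivity version computed from the same items with equipment use scored as unaided, and interpret the standard composite beside it. State the item weights.
- Report independent and equipment life-space descriptively, as measures of aid uptake and not of efficacy.

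The cost is wording in the outcome and analysis sections; no new data are needed. There are two small downsides. Maximal life-space is coarser than the composite. The rescored composite is not the standard score, so it should be supportive only.

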#### Gait assessment

Timed Up and Go test (TUG) evaluate mobility, balance, gait, and risk of falling [15]. In TUG, the researcher requests the participant to stand up on the chair (without using arms), walk 3 meters, go around outside a cone, walk back to the chair, and sit down without using arms [16]. Patients will be instructed to perform the test at the highest possible speed three times and the average of them will be used as the result [16].

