### Sample

Sample size calculation was based on Morgan and cols study, which described a minimal detectable change (MDC_95_) of 8,2 points on Falls Efficacy Scale International (FES-I), with a standard deviation of 12 points [11]. For the calculation, ANOVA sample size was used, and three groups were considered. For an α of 0.05 and a power of 0.80, the total sample size was computed as 42 individuals. Due to the estimated loss of 20% during follow-up, the sample necessary for the success of the study was expanded to 153 individuals, 51 in each group (randomization 1:1:1).

We will include patients aged 65 years or older, admitted to the Geriatric ED of Hospital Sírio-Libanês, willing and able to give informed consent and with at least one of the following for indication and training of mobility aids: reduction of postural instability; improvement of motor control; increase of somatosensory feedback; reduction of biomechanical overload; safe promotion of autonomy; fall history (in the last six months). Exclusion criteria will include altered level of conscience, need for supplemental oxygen (≥3L/min), respiratory distress, hemodynamic instability, postural instability with a tendency to fall backward, cognitive impairment that limits the use of walking aids, hospitalization after ED evaluation, and delirium.

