#### Training of walking aids

Training will be carried out with patients from groups WA and WAT. A physical therapist will identify the mobility needs and will indicate the most appropriate walking aid (cane or walker) considering the following parameters.

Canes: one upper limb used for a walk, light weight-bearing and need for somatosensorial feedback; the cane must be positioned between 15 and 20 centimeters laterally to the feet; the patient’s hand should be supported on the cane at the height of the greater trochanter of the femur and the elbow should be flexed approximately by 30°; in general, the cane is used on the opposite side of the injured leg.Walkers: both upper limbs used to walk, heavy weight bearing, and presence of postural instability; the equipment must be held between 20 and 25 centimeters in front of the body with relaxed shoulders, erect torso, and elbow flexed at 20° to 30°; during the total weight-bearing gait, the walker should be lifted and move forward approximately arm’s length, while one lower limb move forward followed by the other, and the cycle repeats; in a non-weight bearing gait, the walker is lifted and moves forward, then the weight is transferred to the walker through the upper limbs, the affected limb is held in a position anterior to the person’s body, but does not contact the ground, the unaffected limb is moved forward and this cycle repeats.

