### Statistical analysis

Continuous variables will be expressed on average and standard deviation or median and interquartile interval 25%-75%. Categorical data will be presented in absolute and relative numbers. To verify the distribution normality of data, the Shapiro-Wilk normality test will be applied. For comparisons between groups over time, One-way ANOVA test for parametric data or Kruskall-Wallis for non-parametric data will be used. For intragroup analyses, repeated measures Analysis of Variance (RM-ANOVA) test for parametric data or Friedman test for non-parametric data will be used. Only for the Time Up and Go variable before and after intervention, a paired t-test will be used for parametric data, or a Wilcoxon test will be used for non-parametric data. For intergroup and intragroup analyses, the baseline, 3 and 6 months after discharge from the geriatric ED will be considered. To evaluate correlations, the Pearson correlation test will be used for parametric data and the Spearman test will be used for non-parametric data. All the analyses will be carried out using the Statistical Package for Social Sciences (SPSS) version 28.0.1 (SPSS Inc.^®^; Chicago, IL, USA), considering a significance level of 5%.

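### The no-arms Timed Up and Go fits poorly with a sample selected for needing a walking aid, and its within-group paired test covers only those who can do it and cannot attribute a change to the aid

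*Protocol article*

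**What the plan says.** All references are to the Protocol article.

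- **Gait assessment** defines the Timed Up and Go (TUG). The participant must "stand up on the chair (without using arms), walk 3 meters, go around outside a cone", then "walk back to the chair, and sit down without using arms". The test is done "at the highest possible speed three times and the average of them will be used as the result".
- **Sample** enrols people aged 65 or over with at least one indication for a mobility aid. The exclusion closest to this question is "postural instability with a tendency to fall backward". Inability to rise without the arms is not an exclusion, nor is non-weight-bearing status.
- **Training of walking aids** describes walker candidates as "both upper limbs used to walk, heavy weight bearing, and presence of postural instability". It also gives the technique for a gait in which one leg is kept off the ground: "in a non-weight bearing gait, the walker is lifted and moves forward".
- **Assessment moments**: "Assessment of gait speed and fear of falling will be repeated immediately after the intervention". The TUG is the only gait test described. The 3- and 6-month assessments are by telephone or video call and do not include it.
- **Statistical analysis** gives the TUG its own before/after comparison: "a paired t-test will be used for parametric data, or a Wilcoxon test will be used for non-parametric data". The between-group and within-group analyses of the other measures use baseline, 3 and 6 months.

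**The concern.** The test asks for leg strength and balance that some of the people the trial is designed to recruit may not have. A mean of three times has no value for a person who cannot complete one trial, and a paired test uses only people with both a before and an after value. Unless a rule elsewhere intervenes, the TUG result would describe the more able part of the sample without saying so.

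A second weakness does not depend on how many are unable. The only analysis stated for the repeated TUG compares each group with itself. All three groups, control included, receive safe-gait guidance and are then retested. A before/after change in an aid group therefore mixes any effect of the aid with practice, guidance and recovery. The randomised comparison, which would separate these, is not the one named for this measure.

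At stake is the only walking performance test that is repeated after the intervention.

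**Working it through.** There is no TUG figure to reproduce: the article states no TUG effect, standard deviation, power or share unable to perform the test. The check is mainly a reading of the sections against each other.

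**1. What the arm restriction covers.** It applies to rising from the chair and to sitting down. It does not bar the arms, or an aid, during the 3 m walk. The article does not say whether the repeat test is done with the aid.

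**2. Who can be enrolled.** Eligibility rests on an indication for an aid. The walker description includes heavy load through the arms and unstable posture, and the training text provides for a leg that must not be loaded. Only instability with a backward tendency is excluded on this account. People with weak legs, or who may not load one leg, can therefore enter, and for them a hands-free rise and sit at top speed, three times, is the doubtful step.

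**3. What the score and test do with them.** The score is a mean of three times. With no completed trial there is no time, with no time there is no before/after difference, and without a difference the person contributes nothing to a paired t-test.

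**4. What the test can show.** A paired t-test or Wilcoxon test within a group asks whether that group changed. It does not ask whether an aid group changed more than control. The between-group analyses are tied to baseline, 3 and 6 months, and the TUG is not measured at the last two. No comparison between arms is thus stated for the post-intervention TUG.

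**5. How many pairs might remain.** Inputs: 153 participants, 51 per group (Sample), and an assumed unable share u. If unable participants are left blank, pairs left = N × (1 − u), and the detectable difference grows by 1/√(1 − u) with the standard deviation held fixed.

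| u (assumed) | Pairs of 153 | Pairs of 51 per group | 1/√(1 − u) |
|---|---|---|---|
| 5% | 145 | 48 | 1.03 |
| 10% | 138 | 46 | 1.05 |
| 20% | 122 | 41 | 1.12 |
| 30% | 107 | 36 | 1.20 |
| 40% | 92 | 31 | 1.29 |

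The table shows the loss of information for a given share. It says nothing about bias, which would need the TUG change in people who have no TUG.

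**The case against.** The strongest reply has five parts.

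- **The restriction is narrow.** It governs the chair transfers only, so a person who needs a two-handed walker to walk can still obtain a score. This stands. A reader might infer that walker users as a class go unscored; the text does not support that. The difficulty lies with those who cannot rise or sit hands-free. The training section describes technique for each gait pattern and does not suggest that non-weight-bearing patients are common.
- **No hidden benefit is shown.** A reader might infer that the analysis discards those whom the aid helps most and so pulls the mobility effect towards zero. The documents do not support this either. The no-arms rule applies equally at the retest, and a cane or walker does not help anyone rise without using the arms. A move from unable to able would hardly arise by that route. Any simulated loss would rest on conversion rates that the article does not give.
- **Dropping is not stated.** No section says that non-completers go unscored. A rule may sit in the full protocol or analysis plan, and a Wilcoxon test could take a worst-value code. This stands as a caution, and the consequence is worded conditionally here. But the no-arms instruction, the mean-of-three score and the within-group test are stated choices, not omissions.
- **The consequence is limited.** Fear of falling is primary. The mobility measure named as a secondary outcome is the life-space assessment, and the TUG is not named individually in the outcome list. This stands.
- **The test version is a sourced choice.** The article cites a reference for its TUG procedure, and changing it costs comparability. That is true, but a published procedure can still be unsuitable for a sample selected for needing support.

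**Conclusion.** The point holds in a limited form. The TUG as defined is a poor fit to part of the eligible sample. If those unable to do it have no time, the before/after result describes only participants able to do the test. Separately, and whatever the share unable, the stated within-group test cannot attribute a TUG change to the aid.

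The size is unknown. Under an assumed 5% to 40% unable, and if their results are left blank, between 8 and 61 of 153 pairs would be lost (153 − 145 and 153 − 92). Neither the size nor the direction of any bias follows from the documents. The FES-I is untouched, so this is worth correcting but does not threaten the trial's main conclusion.

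**What to change.** Reconcile Gait assessment, Training of walking aids and Statistical analysis on four points:

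1. Use one TUG test condition in all arms, at both times, that the eligible sample can attempt; for example, arm use allowed and recorded. Record at each test whether an aid was used.
2. Keep participants who cannot complete the test in the analysis as the worst rank, below every observed time.
3. Compare arms on the ranked post-intervention result with baseline rank as a covariate. The paired within-group results can remain as description.
4. Report the proportion completing the test before and after, by arm.

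The cost is a change to the test instruction, two extra data fields (arm use and aid use) and a rank-based analysis, with no additional visit or procedure. There are two small downsides: times become less comparable with references that forbid arm use, and the effect is no longer a simple difference in seconds. The one-minute sit-to-stand under Functional capacity, done with hands on the hips, raises the same feasibility question and can be checked at the same time.
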